# STATEMENT OF COMPLIANCE

This document is a protocol for a clinical research trial study involving the human participants. The trial will be conducted in accordance with International Conference on Harmonisation Good Clinical Practice (ICH GCP E6 (R2)), Health Canada Division 5 (Part C, Division 5 of the Food and Drug Regulations “Drugs for Clinical Trials Involving Human Subjects”), and applicable regulatory requirements.

The protocol, informed consent form(s), recruitment materials, and all participant materials will be submitted to the REB for review and approval. Approval of both the protocol and the consent form must be obtained before any participant is enrolled. Any amendment to the protocol will require review and approval by the REB before the changes are implemented to the study. All changes to the consent form will be REB approved; a determination will be made regarding whether a new consent needs to be obtained from participants who provided consent, using a previously approved consent form.

# PROTOCOL SUMMARY

## Synopsis

| Title | A Multi-Centre, Tolerability Study of a Cannabidiol-enriched Cannabis Herbal Extract for Chronic Headaches in Adolescents: the CAN-CHA trial |
| --- | --- |
| Short Title | Cannabis for Chronic Headaches in Adolescents (CAN-CHA) |
| Protocol Number | CAN-CHA |
| Version Number | 6.0 |
| Phase | 2 |
| Study Drug | MediPharm Labs MPL-001, CBD:THC 50:2 (50mg of CBD per ml to 2mg of THC per ml, dissolved in medium chain triglycerides oil derived from fractionated palm oil) with a lemon peppermint flavouring 1500mg of total CBD per 30ml bottle |
| Treatment Regimen | MediPharm Labs MPL-001, CBD:THC 50:2, will be used as a study Intervention. Study participants will receive escalating doses of CBD starting at 0.2-0.4 mg/kg/day up to 0.8-1 mg/kg/day followed by a weaning period. Dosed twice a day orally |
| Study Design | A multicenter, open-label, dose-escalation study will be conducted across three centres in Canada to study the safety, tolerability, and effectiveness of a CBD-enriched CHE in adolescents with chronic headaches. The study will consist of four different phases: recruitment, baseline (1 month), treatment (4 months) and weaning (1 month). |
| Study Duration | The participants will be enrolled in the study for 6 months and complete 7 study visits. The overall study is expected to be completed within 24 months.  Recruitment/Screening  Baseline: 1 month, Treatment: 4 months, Weaning: 1 month |
| Objectives | **Primary Objective**: To determine the safety and tolerability of escalating doses of a Cannabidiol (CBD)-enriched Cannabis Herbal Extract (CHE) in adolescents with chronic headaches.  **Secondary Objectives:**   1. To investigate the relationship between the dose-escalation with headache-free days. 2. To monitor the effect of CBD-enriched CHE oil on the intensity of pain related to chronic headaches. 3. To evaluate the effect of CBD-enriched CHE oil on sleep, mood and function in adolescents with chronic headaches. 4. To explore the impact of chronic headaches on quality of life   **Exploratory Objectives:**   1. To investigate the relationship between the dose-escalation and steady-state trough levels of bioactive cannabinoids. 2. To investigate the relationship between pharmacogenetic variations and response outcomes in adolescents receiving CBD-enriched CHE oil. |
| Endpoints | **Primary Endpoint:**  The frequency and type of treatment-emergent adverse events among participants treated with CBD-enriched CHE reported daily and evaluated monthly before the subsequent dose escalation  **Secondary Endpoints:**   1. Number of headache-free days per month. 2. Percentage change in average daily pain intensity due to headache on the numeric rating scale (NRS) from baseline to each follow up visit. 3. Sleep, mood and function are to be reported using the percentage change in the scores of PROMIS (patient-reported outcome measurement information system) measures from the Pediatric Item Bank:    1. Pediatric Sleep-related Impairment – Short Form 8a    2. Pediatric Short Form v2.0 - Anxiety - 8a    3. Pediatric Short Form v2.0 - Depressive Symptoms 8a    4. Pediatric Pain Interference – Short Form 8a    5. Pediatric Positive Affect – Short Form 8a    6. Self-directed goal attainment will be reported as a percentage toward a physical, mental and social goal reported by participants at each monthly visit. 4. Family impact scores will be reported by PedsQL™ Family Impact Module, Version 2.0 and compared with baseline scores.   **Exploratory Endpoints:**   1. Steady-state plasma levels of bioactive cannabinoids, namely THC, CBD, 11-OH-THC, 7-OH-CBD, and Cannabichromene, during each follow up visit before dose escalation. 2. Genetic polymorphisms of genes encoding for CYP enzymes and the p-glycoprotein transporter and plasma levels of THC, CBD and their active metabolites in the study participants. |
| Number of Participants | 20 participants |
| Inclusion Criteria | Adolescent patients of the qualified investigator between the ages of 14-17 years with chronic headaches will be enrolled.  They must have headaches (migraine or tension-like features) on more than 15 days per month for more than 3 months and have failed at least two treatment options for either tolerability or efficacy.  Participants must be committed to using contraception, abstaining from recreational cannabis use, and working with psychology and physiotherapy teams as appropriate. |
| Statistical Methodology | *Sample Size determination:*  Precedent suggests that a power calculation is not appropriate for a dose-finding study. The study site and the number of planned dose escalations are standard for clinical trials.  *Populations for Analyses:*  We will complete an intent to treat analysis. All participants who received the investigational product for at least one month will be included in the analysis to ensure that these data would be likely to represent the effects of the study intervention.  *Safety Analyses:*  The severity, frequency, and relationship of AEs to study intervention will be presented by System Organ Class (SOC). The start date, stop date, severity, relationship, expectedness, outcome, and duration of each AE will be reported. Serious treatment-emergent AEs will be presented either in a table or a listing.  *Baseline and Descriptive Statistics:*  We will perform the descriptive statistics to describe baseline characteristics and other outcomes. The proportions and frequencies will be used to categories the categorical variable. The mean, median, range or standard deviations will be used to categories the continuous endpoints. Subgroup summarization based on dose level or other criteria may also be conducted. Median concentrations of CBD, THC and the major metabolites will be reported with ranges for each sampling time point. The ratio of parent to metabolites will be reported to provide estimates of the variability in cannabinoid metabolism.  *Sub-Group Analyses:*  We will perform prespecified subgroup analysis of primary and secondary outcomes-based sex and dose. |

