# STATISTICAL CONSIDERATIONS

## Statistical Hypotheses

The primary endpoint (adverse events) will be analysed and presented descriptively with frequency counts and severity criteria. There are no pre specified statistical hypothesis.

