## Sample Size Determination

The CAN-CHA trial is a tolerability study designed to identify a safe dose of a cannabis product in adolescents with chronic headache. Because of the within-participant study design, a sample size of 20 study participants should provide a reasonable characterization of the pattern of adverse event frequency and severity as dosage increases. To provide more generalizable data, we will recruit these 20 study participants across three chronic pain programs in Halifax, Vancouver, and Toronto.

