## Populations for Analyses

The following study populations are defined and will be analyzed as specified below.

Intention to treat population: We will complete an intent to treat analysis by which all participants who received at least one dose of the lowest dose of investigational product, whose dosing went off the track, lost to follow up, non-compliance, protocol deviation, and withdrawal.

Any study participant on this trial (registered) but never got study treatment will be mentioned, including the reason(s) of their exclusion from the trial.

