### Baseline Descriptive Statistics

The primary statistical analysis will be a descriptive summary of the pattern of incidence and severity of adverse events across dosage levels. Conventional summary statistics will describe baseline characteristics and other outcomes (means, standard deviations, and medians, range and interquartile range (IQR) for numerical variables; counts and percentages for categorical variables). Summaries will be provided both overall and by dosage level. Medians, ranges and IQR, will be provided for the concentrations of CBD, THC and the primary metabolites at each sampling point. The ratio of parent compound concentration to metabolites will also be summarized to explore variability in cannabinoid metabolism. System organ class will present the severity, frequency, and relationship of treatment-emergent AEs to study intervention. The start date, stop date, severity, relationship, expectedness, outcome, and duration of each AE will be reported. Serious treatment-emergent AEs will be presented either in a table or a listing. The secondary outcomes, including pain, sleep impairment, depression, positive affect, anxiety and goal attainment scores, will be summarized at each timepoint; change from baseline will also be reported (both absolute and percentage change).

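### The synopsis restricts the intent-to-treat set to participants with at least one month on product, which contradicts section 10.3 and removes early intolerance from the primary safety summary

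*Protocol*

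**What the plan says.** The Statistical Methodology row of the Synopsis announces "We will complete an intent to treat analysis" and then states the inclusion rule: "All participants who received the investigational product for at least one month will be included in the analysis". The reason given is that such data are more likely to reflect what the intervention does. The Safety Analyses text in the same row names no other population.

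Section 10.3 (Populations for Analyses) also defines an intention-to-treat population, but as "all participants who received at least one dose of the lowest dose of investigational product". It goes on to name participants "whose dosing went off the track, lost to follow up, non-compliance, protocol deviation, and withdrawal". That sentence has no closing verb, but it reads as a list of people to be kept. Only registered participants who never received treatment are set apart, to be mentioned with reasons.

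The primary endpoint in the Synopsis is "The frequency and type of treatment-emergent adverse events among participants treated with CBD-enriched CHE". Section 10.3.2 says "The primary statistical analysis will be a descriptive summary of the pattern of incidence and severity of adverse events across dosage levels". Neither 10.3.1 nor 10.3.2 names an analysis set, and no safety population is defined anywhere in the protocol.

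**The concern.** The trial's primary objective is safety and tolerability. A minimum-exposure rule may have some logic for describing effectiveness or drug levels. For tolerability it conditions on the result, because being able to stay on the product for a month is part of what is being measured.

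If the Synopsis rule is applied, a participant who stops within the first month because of adverse effects is not counted, and neither are that participant's events. Tolerability then looks better than it was. The protocol says the tolerated dose found here will inform a later randomised trial, so the bias would carry forward.

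There is also a problem of choice. The trial is open-label, and with two rules under one name the set could be picked after the early withdrawals are known.

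**Working it through.** **No planned figure to reproduce.** Section 10.1 says "There are no pre specified statistical hypothesis", and section 10.2 justifies the size only by saying that "a sample size of 20 study participants should provide a reasonable characterization of the pattern of adverse event frequency and severity". The check is therefore a comparison of the texts, followed by an illustration of the consequence.

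**The two rules side by side**

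| | Synopsis | Section 10.3 |
|---|---|---|
| Label | Intent to treat | Intention to treat |
| Exposure needed | At least one month | At least one dose |
| Stops on day 10 of product | Out | In |
| Stops in treatment month 2, 3 or 4 | In | In |
| Never dosed | Out | Out, mentioned with reasons |

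Everyone starts at the lowest dose level, so the 10.3 criterion amounts to all dosed participants.

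**Why the difference reaches the primary result**

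- Table 4: the first dose level lasts one month, the same length as the Synopsis threshold.
- Participant Discontinuation/Withdrawal from the Study: participants may leave at any time, and may be withdrawn for intolerable adverse effects, with no minimum time on product.
- Same section: treated participants who withdraw are not replaced, so the denominator shrinks.
- Schedule of Activities, footnote a: those who stop product but stay in the study are followed to visit 7. The Synopsis rule depends on product received, so it would leave out their data as well.

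**Direction.** Let x of 20 dosed participants have a given event, and suppose k stop within month 1, all of them with that event. The two proportions are x/20 and (x − k)/(20 − k). Their difference is

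x/20 − (x − k)/(20 − k) = k(20 − x) / [20(20 − k)],

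which is never negative. The one-month set is therefore never less favourable in this case. If some early leavers stop for unrelated reasons and without the event, the direction depends on whether the event is more common among early leavers than among those who stay.

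**Size.** The protocol gives no first-month stopping rate; the counts below are assumptions. The proportion shown is participants stopping for intolerance, with exact (Clopper-Pearson) 95% intervals. For 0 of n the upper limit is 1 − 0.025^(1/n); for n = 17 this is 19.5%.

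| Stops in month 1 | Later stops | At least one dose | At least one month |
|---|---|---|---|
| 2 | 0 | 2/20 = 10% (1.2% to 31.7%) | 0/18 = 0% (0% to 18.5%) |
| 3 | 0 | 3/20 = 15% (3.2% to 37.9%) | 0/17 = 0% (0% to 19.5%) |
| 2 | 2 | 4/20 = 20% (5.7% to 43.7%) | 2/18 = 11.1% (1.4% to 34.7%) |

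The formula agrees: x = 3, k = 3 gives 3 × 17 / (20 × 17) = 15 points; x = 4, k = 2 gives 2 × 16 / (20 × 18) = 8.9 points.

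**How often the sets would differ.** With first-month stopping probability p, the chance of at least one exclusion among 20 is 1 − (1 − p)^20.

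| Assumed p | Expected exclusions (20p) | Chance of at least one |
|---|---|---|
| 5% | 1 | 64% |
| 10% | 2 | 88% |
| 15% | 3 | 96% |
| 20% | 4 | 99% |

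**The case against.** The best reply is that this is a loose synopsis sentence, that the dedicated populations section has the sensible rule, and that the trial is descriptive with no hypothesis to distort. The endpoint's reference to treated participants also fits the one-dose set. All adverse events from consent to visit 7 are recorded, withdrawal reasons go on the case report form, and section 10.3.4 lists individual data, so early events are not lost from the record.

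Several of these points stand and limit the scope:

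- Only stops before one month on product are affected. Intolerance at the higher dose levels is counted under both rules.
- A dose-limiting toxicity bars escalation but does not by itself end treatment, so someone who has one and stays on product for the month remains in both sets.
- The Synopsis does not say outright that early stoppers leave the safety analysis. This follows from its giving one population for the analysis while no safety set exists.
- The worked proportions concern stopping for intolerance, whereas the endpoint is the frequency and type of adverse events. The case with no later stops gives the starkest contrast.

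The contradiction remains. Records and listings do not put early stoppers back into the numerator and denominator of a summary table, and in a descriptive trial those tables are the primary result. A separate analysis plan could choose one rule, but would then contradict the other half of the protocol.

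**Conclusion.** The concern holds and should be fixed. The current protocol states two incompatible rules under one label, and the Synopsis rule is the wrong one for a safety endpoint because it selects on tolerability.

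The size depends on how many participants stop in month 1, which the protocol does not give. Under the assumptions above, two or three such stops among 20 move the reported proportion stopping for intolerance by about 9 to 15 percentage points, always in the favourable direction. The two sets are more likely than not to differ even at an assumed 5% first-month stopping rate. If nobody stops in month 1, the sets coincide and nothing is lost.

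**What to change.** 1. Delete the one-month sentence and its rationale from the Synopsis.
2. In the Synopsis and in section 10.3, define one set, all participants who took at least one dose of MPL-001. State that it is used for every adverse event and tolerability summary.
3. Complete the unfinished sentence in section 10.3 so that it says plainly that participants who withdraw, are lost to follow-up, do not comply or have deviations are included.
4. Name that set in sections 10.3.1 and 10.3.2.
5. If a set with at least one month of exposure is wanted for effectiveness or drug-level summaries, keep it as supplementary, do not call it intent to treat, and list those left out with reasons.

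The cost is a few sentences in a protocol amendment, with no extra data, visits or participants. If there are early stops, reported tolerability will look less favourable than under the Synopsis rule, but it will describe everyone who was exposed.

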## Schema

[figure not shown]

**Figure 1:** A flow chart of participant enrollment, treatment with CBD-Enriched CHE, monitoring and weaning

## Schedule of Activities (SoA)

**Table 1.** CAN-CHA schedule of activities

| Study visit # | **1**  (Baseline) | **2** | **3** | **4** | **5** | **6** | **7** |
| --- | --- | --- | --- | --- | --- | --- | --- |
| Day # | **1** | **30** | **60** | **90** | **120** | **150** | **180** |
| Follow up window (days) | **±5** | **± 5** | **± 5** | **±5** | **± 5** | **±5** | **± 5** |
| Informed Consent | X |  |  |  |  |  |  |
| Demographics | X |  |  |  |  |  |  |
| Medical history (safety screening with SCR Checklist)^b^ | X |  |  |  |  |  |  |
| Review ongoing co-existing medical conditions^d^ |  | X | X | X | X | X | X |
| Concomitant medication and therapy review | X | X | X | X | X | X | X |
| IP intervention follow-up^a^ |  | X^a^ | X^a^ | X^a^ | X^a^ | X^a^ |  |
| Intervention dose of CBD (mg/kg/day) |  | 0.2- 0.4 | 0.4-0.6 | 0.6-0.8 | 0.8-1.0 | Wean |  |
| Physical exam | X |  |  |  |  |  | X |
| Vital signs and weight^c^ | X | X | X | X | X | X | X |
| Pregnancy test in females^e^ | X | X | X | X | X | X | X |
| Assign Daily eDiary via REDCap | X |  |  |  |  |  |  |
| Review of Daily Diary |  | X | X | X | X | X | X |
| Review of Adverse Events |  | X | X | X | X | X | X |
| Review of Cannabis-related Adverse Event |  | X | X | X | X | X | X |
| Cannabis Use Disorder Identification Test Short-Form (CUDIT-SF) | X |  |  |  |  |  | X |
| Pediatric Sleep-Related Impairment– Short Form 8a Scale | X | X | X | X | X | X | X |
| PedsQL Family Impact | X | X | X | X | X | X | X |
| Pediatric Short Form v2.0 - Anxiety - 8a scale | X | X | X | X | X | X | X |
| Pediatric Short Form v2.0 - Depressive Symptoms 8a scale | X | X | X | X | X | X | X |
| Pediatric Pain Interference – Short Form 8a scale | X | X | X | X | X | X | X |
| Pediatric Positive Affect – Short Form 8a | X | X | X | X | X | X | X |
| Self-directed goal attainment | X | X | X | X | X | X | X |
| Participant Trial Expectation Survey | X |  |  |  |  |  | X |
| Blood samples (8mLs, approx.) | X | X | X | X | X | X | X |
| Saliva Sample for Pharmacogenomics | X |  |  |  |  |  |  |
| Electrocardiogram (if not done in the last 3 months) | X |  |  |  |  |  |  |
| Drug Accountability |  | X | X | X | X | X | X |
| Visit duration (minutes) | 60 | 45 | 60 | 45 | 60 | 45 | 60 |

*a. If participant withdraw from the study intervention prior to visit 7 but consents to stay in the study, they will be followed up till visit 7 for all the other assessments, including bloodwork, eDiary and questionnaires. Site study team will provide guidance on IP administration and follow up with participant regarding their experience of IP administration at home. IP administration will not be completed at study site during the scheduled study visit.*

*b. Document titled “C4T Baseline Safety Screening Tool for Cannabis-related interventional trials”, also called “SCR Checklist” will be used by study team to document thorough medical history at visit 1, with Common Terminology Criteria for Adverse Events (CTCAE) grade level to be applied with each reported medical history condition.*

*c. Participants will self-administer the investigational product orally following a dosing calendar and all dosing calculations will be based on weight at baseline (visit 1), unless there is a significant body weight change that would affect dosing. If participant’s body weight increases or decreases for 10% or above comparing with baseline data, site investigator will contact study PI [name] for further instructions regarding dose change or participant withdrawing. The decision will be made on a case-by-case basis to protect participant’s safety, and in the meanwhile minimize negative impact on data integrity.*

*d. Any ongoing co-existing medical condition at visit 1 will be followed up by site study team at follow-up visits to document changes.*

*e. Both urine and blood pregnancy tests will be completed at visit 1. Blood pregnancy test will be completed from visit 2- visit 7.*

# INTRODUCTION

## Study Rationale

Randomized Control Trials (RCTs) and open-label studies have demonstrated the well-defined margin of safety and efficacy of CBD and CBD-enriched CHE in children with intractable epilepsy.[[1-9](#_heading=h.184mhaj)] Chronic headaches are one of the most common pain syndromes in adolescence, and despite numerous treatment options, roughly only half of adolescents with Chronic Headache (C) experience remission. CBD and other cannabis products are being used off-label for the treatment of chronic headaches. [[10](#_heading=h.3jtnz0s)] Prescription cannabinoids (nabiximols) and other cannabis-based products containing THC are currently being used off-label in adolescents with chronic headaches. The overall purpose of this open-label phase 2 study is to generate clinical evidence on the safety, and tolerability of a CBD-enriched CHE in adolescents suffering from chronic headaches. Furthermore, the ideal tolerated dose derived from this study will inform a future RCT to explore the efficacy of CBD-enriched CHE in a larger cohort. In this study, participants will receive escalating doses to a maximum of 1.0mg/kg of CBD/day to treat the chronic headaches. There have been many historical challenges with studying cannabis products and cannabinoids due to difficulties in consistently obtaining products, variable quality control and stigma associated with cannabis. Canada has the opportunity to be a world leader in cannabis research. The successful outcomes from this research project have the potential to create a meaningful impact on the lives of Canadian adolescents, given the high prevalence of chronic headaches, severe morbidity, and the current lack of effective treatment options.

